#### Polygenic Risk Score (PRS)

2.3.4

At baseline, a venous blood sample is collected, processed, and genomic DNA extracted at Biobanking Victoria, Precision Medicine, Monash University. Genotyping is performed using the Confluence array (Illumina, CA, USA), and PRS calculated at The Broad Institute as described previously [27]. The PRS report (Figure 3b), co‐designed with Monash Health consumer representatives, uses simple language and visual aids, such as a bell curve, to contextualize individual risk relative to the general population. Co‐design focused on presenting genomic data clearly while maintaining scientific accuracy to support understanding and informed decision‐making.

#### Risk Factor Counseling

2.3.5

Risk factor counseling is delivered either in‐person or via telehealth, depending on participants preference, by a trained study nurse. Advice follows recommendations from the International Diabetes Federation [28], American Heart Association Life Essential 8 [29], Diabetes Australia [30], and the Heart Foundation [31]. Motivational interviewing (MI) techniques are used to encourage health‐promoting behaviors and adherence to therapies. MI was selected for its proven ability to foster intrinsic motivation and sustainable behavior change, empowering participants to identify their own reasons for change and enhancing long‐term commitment [32]. Participants in Groups 1 and 2 receive their CTCA or PRS results at initial consultation, with reinforcement at a 6‐month follow‐up. Sessions also involve setting SMART (Specific, Measurable, Achievable, Relevant, Time‐bound) goals to support cardiovascular risk factor modification. Key components are outlined in Table 2.

**Table 2 clc70363-tbl-0002:** Key Components of the intervention.

Components	Description
Health Education	Smoking Cessation: Assess willingness to quit; provide counseling and resources; with consent, refer to Quitline Diet: Review current habits; promote healthy proteins, more vegetables/fruits, low‐GI foods, nutritious snacks, and portion control Physical Activity: Encourage ≥ 150 min/week moderate‐intensity exercise; discuss personalized activity options
Engagement with Allied Health Professionals	Review current engagement; encourage visits to dietitian, exercise physiologist, and diabetes educator for tailored plans, and to podiatrist and optometrist for preventive care
Cardiovascular Risk Assessment	Calculate 5‐year CVD risk using the New Zealand Society for the Study of Diabetes CVD Risk Assessment calculator, which incorporates diabetes duration, glycated hemoglobin, blood pressure, lipid profile, urine albumin‐creatinine ratio, and antihypertensive use

Abbreviation: CVD, cardiovascular disease.

### Outcomes

2.4

The primary objective is to assess the impact of personalized cardiovascular risk information, derived from CTCA and PRS, on cardiovascular risk factor modification in individuals with T2D (Table 3). The primary outcome is change in non‐calcified plaque volume on CTCA at 12 months. Non‐calcified plaque volume was selected because it reflects a more biologically active component of coronary atherosclerosis and may be more responsive to risk factor modification over relatively short timeframes.

**Table 3 clc70363-tbl-0003:** VOLTAIRE trial objectives and outcomes.

Primary outcome
– Change in non‐calcified plaque volume
Secondary outcomes
– Achievement of an LDL‐C < 1.8 mmol/L – Intensification of lipid‐lowering therapy, defined as any of the following—increase in the intensity of statin prescribed, addition of ezetimibe, PCSK‐9i – Prescription of a guideline‐recommended statin – Reporting of high levels of adherence to their lipid‐lowering therapy – Level of patient activation and engagement in their care during the study period, compared with baseline – Mental health responses (psychological and emotional reactions) after receiving PRS or CTCA results, including personal perceived risk, personal perceived health‐related quality of life, anxiety, depression or other mental health issues – Change in 5‐year CVD risk
Exploratory outcomes
– Incidence of cardiovascular events – Achievement of all three modifiable risk factor goals: LDL‐C < 1.8 mmol/L, systolic blood. pressure ≤ 130 mmHg, and smoking cessation – Change in hsCRP – Change in HbA1c – Changes in additional imaging parameters, including total atheroma volume, calcified plaque volume, percent atheroma volume, PCAT and epicardial fat volume and density – Achievement of an LDL‐C < 1.8 mmol/L at any time during follow up
Implementation outcome
– Appropriateness, feasibility, and acceptability of the CTCA or the PRS intervention from participants' perspectives

Abbreviations: AE, adverse event; CTCA, computed tomography coronary angiography; CVD, cardiovascular disease; HbA1c, glycated hemoglobin A1c; hsCRP, high‐sensitivity C‐reactive protein; LDL‐C, low‐density lipoprotein cholesterol; PCAT, pericoronary adipose tissue; PCSK‐9i, proprotein convertase subtilisin/kexin type 9 inhibitors; PRS, polygenic risk score.

Secondary outcomes include the achievement of Low‐density lipoprotein‐cholesterol (LDL‐C) levels below 1.8 mmol/L at 12 months, intensification of lipid‐lowering therapy, prescription of guideline‐recommended statins, and adherence at 6 and 12 months. Additional measures include changes in patient activation (PAM‐13), psychological health (depression, anxiety, perceived risk, quality of life), and 5‐year CVD risk scores.

Exploratory outcomes include major cardiovascular events (e.g., all‐cause death, myocardial infarction or stroke), achievement of modifiable risk factor targets (LDL‐C < 1.8 mmol/L, systolic BP ≤ 130 mmHg, and smoking cessation), changes in biomarkers (HbA1c, hsCRP), and other imaging parameters (total atheroma volume, calcified plaque volume). Implementation objectives assess the appropriateness, feasibility, and acceptability of the CTCA or PRS intervention from participants' perspectives.

### Randomization and Blinding

2.5

Participants are randomized (1:1:1) using a computer‐generated random sequence with allocation concealment, conducted by research staff not involved in participant interactions to prevent selection bias. Outcome assessors are blinded to minimize analysis bias. Due to the nature of the interventions, participants and their treating clinicians are not blinded; however, site staff remain blinded to imaging results in non‐CTCA groups and PRS results in non‐PRS groups.

### Data Collection

2.6

Data collection includes comprehensive assessments at baseline, 6 months, and 12 months, covering socio‐demographic, clinical, behavioral, and psychological measures. Details of all assessments, including timelines and specific parameters, are provided in Table S1.

### Statistical Analysis

2.7

#### Sample Size Calculation

2.7.1

The sample size was determined based on the objective to compare progression rates across the three groups. A total of 30 participants per treatment group (total *n* = 90) is required to undergo serial, evaluable imaging. This sample size provides 80% power to detect a difference in the progression of non‐calcified plaque volume between a pair of groups of 8 mm^3^, assuming a standard deviation of 11 mm^3^, a Bonferroni‐adjusted alpha of 0.83%, and that baseline adjustment accounts for one‐third of outcome variability.

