### Participants

2.2

Inclusion criteria were age ≥ 40 years, T2D managed with lifestyle modification or glucose‐lowering medication, and no history of clinically manifest CVD. Participants required acceptable imaging quality as determined by the Victorian Heart Institute Atherosclerosis Imaging Core Lab (VHI‐AICL).

Exclusion criteria included inability to provide written informed consent, unwillingness to undergo serial evaluation, or clinically manifest CVD. Participants with significant coronary disease on baseline CTCA (≥ 50% stenosis in the left main or ≥ 70% in any epicardial artery) were excluded for safety, as masking would not be possible. Individuals unable to complete study procedures, in the investigator's opinion, were also excluded (Table 1).

**Table 1 clc70363-tbl-0001:** VOLTAIRE eligibility criteria.

Inclusion criteria	Exclusion criteria
Age 40 years or older, Established diagnosis of type 2 diabetes, No history of clinically manifest CVD, Having acceptable imaging quality as deemed by the VHI‐AICL	Unable to provide written informed consent Unwilling to be followed for serial evaluation Clinically manifest CVD Clinically significant coronary disease on CT coronary angiogram (≥ 50% in the left main coronary artery or ≥ 70% in any epicardial coronary artery) Unable to participate in the study or complete protocol required assessments in the opinion of the Investigator

Abbreviations: CTCA, computed tomography coronary angiography; CVD, cardiovascular disease; VHI‐AICL, Victorian Heart Institute Atherosclerosis Imaging Core Lab.

Recruitment ran from August 2023 to June 2025, enrolling 147 participants, with 79 randomized: 26 to the CTCA group, 27 to the PRS group, and 26 to the control group.

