The VOLTAIRE trial also addresses broader health needs by screening for depression, anxiety, diabetes distress, and sleep apnoea, with referral of severe cases to GPs. This integrated approach recognizes the interplay between physical and psychological health. Recruitment through community GP clinics, diabetes support groups, social media, and local university campuses supported enrollment of a broader and more diverse cohort.

This study should be interpreted considering several limitations. The single‐center design may limit generalizability to other populations and settings, and hospital‐based enrollment may still have preferentially included individuals who were more engaged with healthcare, which could have influenced responsiveness to the interventions. Given the open‐label design, performance bias cannot be excluded, as participants and clinicians were aware of group allocation. The modest sample size was powered for the primary mechanistic endpoint but may have limited statistical power for some secondary and exploratory outcomes. Larger, adequately powered multicentre studies are needed to confirm these findings.

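### Recruitment closed with 79 randomised against 90 evaluable scan pairs required, so the Discussion's claim that the sample was powered for the primary endpoint is wrong for the trial as conducted

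*Protocol article*

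**What the plan says.** Section 2.7.1 (Sample Size Calculation) states the requirement as a count of people with usable paired scans: 30 in each group, 90 overall, is the number that "is required to undergo serial, evaluable imaging". On power, the section says: "This sample size provides 80% power to detect a difference". The target is a gap of 8 mm³ in non-calcified plaque progression for any two groups compared. The remaining inputs are an SD of 11 mm³, a per-comparison alpha of 0.83% after Bonferroni correction, and one-third of the outcome variability removed by baseline adjustment. Section 2.7.2 specifies two-sided tests.

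Section 2.2 (Participants) reports in the past tense that recruitment ran from August 2023 to June 2025 and enrolled 147 people, "with 79 randomized: 26 to the CTCA group, 27 to the PRS group, and 26 to the control group".

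Section 2.3.2 gives the repeat scan at 12 months only to those randomised. Section 2.3.3 excludes scans that cannot be interpreted.

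The Discussion, in its limitations paragraph, says: "The modest sample size was powered for the primary mechanistic endpoint". It concedes limited power only for some secondary and exploratory outcomes.

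**The concern.** These statements cannot all describe the same trial. The requirement is 30 evaluable scan pairs per group, and every group closed below 30 before any loss. The 68 people enrolled but not randomised (147 − 79) cannot make up the difference, because they have no 12-month scan. The article does not mention the shortfall or restate the power, and it still tells the reader that the primary endpoint was adequately powered.

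What is at stake is how the primary result is read. Taken at face value, the article implies a 20% chance of missing a true 8 mm³ difference in a given pairwise comparison. At the sizes randomised, that chance is about 27-31% with every scan usable, and higher if scans are lost.

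**Working it through.** **Inputs.** From section 2.7.1: difference 8 mm³, SD 11 mm³, alpha 0.83% per pairwise comparison, one-third of variance explained by baseline, 30 per group. From section 2.7.2: two-sided tests. From section 2.2: 26, 27 and 26 randomised.

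**Formulas.** Residual SD = 11 × √(1 − 1/3) = 8.98. SE of a pairwise difference = 8.98 × √(1/n₁ + 1/n₂). Standardised effect = 8 / SE. Normal-approximation power = Φ(8/SE − 2.640), where 2.640 is the two-sided 0.83% critical value. The t-based power uses a noncentral t distribution with the residual variance pooled over three groups and degrees of freedom equal to the total number minus 4 (three group means and one baseline slope).

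**Step 1: reproduce the article's figure.** At 30 per group, SE = 8.98 × √(2/30) = 2.319 and 8/SE = 3.450. Normal: Φ(3.450 − 2.640) = 79.1%. t with 86 df: 77.0%. Solving for n at 80% power by the normal approximation gives 30.55, so 31 per group when rounded up. The stated 30 per group and 80% are reproduced within rounding, and the normal approximation comes closest.

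**Step 2: the numbers randomised, with every scan evaluable.** 26 + 27 + 26 = 79, which is 11 short of 90 (88% of target).

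| Comparison | SE | 8/SE | Power, normal | Power, t |
|---|---|---|---|---|
| 30 v 30 (planned) | 2.319 | 3.450 | 79.1% | 77.0% |
| 26 v 27 | 2.468 | 3.242 | 72.6% | 70.1% |
| 26 v 26 | 2.491 | 3.212 | 71.6% | 69.0% |

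For 26 v 26, the like-for-like loss is 79.1 − 71.6 = 7.5 points (normal) or 77.0 − 69.0 = 8.0 points (t).

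**Step 3: difference detectable with 80% power.** By the normal approximation this is (2.640 + 0.842) × SE. At 30 per group it is 3.482 × 2.319 = 8.07 mm³, and at 26 per group 3.482 × 2.491 = 8.67 mm³. With the t reference the figures are 8.24 and 8.88 mm³. Either way the increase is about 0.6 mm³.

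**Step 4: scan loss.** The article gives no loss rate, so the rates here are assumptions. A loss of 10% from 26 leaves about 23 per group, and 15% leaves about 22.

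| Evaluable per group | Assumed loss | Power, normal | Power, t |
|---|---|---|---|
| 23 | about 10% | 64.8% | 61.8% |
| 22 | about 15% | 62.3% | 59.2% |

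**The case against.** **The sample size section is not wrong.** This stands. It says what 30 evaluable per group provides, and that figure reproduces. A reader might infer an arithmetic error in section 2.7.1, but there is none. The fault lies in the Discussion sentence set against the number randomised.

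**The loss is smaller than it first looks.** This also stands. A reader might set a t-based 69% beside the stated 80% and conclude that 11 points were lost. The stated 80% matches the normal approximation, and the t method gives only 77% at the planned size. Compared within one method, the loss is 7 to 8 points before scan loss.

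**The 0.83% might be one-sided, equivalent to 1.67% two-sided.** On that reading, 26 v 26 and 26 v 27 with no loss give 79.3% and 80.2% by the normal approximation, or 77.5% and 78.4% with the t reference, so there would be almost no shortfall until scans were lost. The article does not support this reading. It specifies two-sided tests, and at 30 per group that level would give 85%, not the stated 80%.

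**"Was powered" may describe the design.** The words allow it. But the sentence is about the trial's modest sample size, sits among the limitations, and appears in an article that reports recruitment as finished at 79. Most readers will apply it to the trial as run.

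**The article is already cautious.** It calls the sample modest and asks for larger studies. That is fair, but the caution about power is confined to secondary and exploratory outcomes. A reader might also infer that the authors will present a non-significant result as evidence of no effect. Nothing in the article says so.

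**Conclusion.** The point holds for the Discussion sentence. Ninety evaluable scan pairs cannot be reached, and the power for the primary pairwise comparisons is below the planned 80%. It is at most about 72-73% (normal) or 69-70% (t), against 79% or 77% at 30 per group by the same method. With an assumed 10-15% scan loss it would be about 62-65% (normal) or 59-62% (t).

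These figures rest on the article's own difference, SD and variance reduction, and on a two-sided 0.83% level. The no-loss figures are upper limits under those inputs.

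The shortfall is moderate. It does not bias the estimated effect, alter the type I error or invalidate the planned analysis, and the documents give no ground for saying that it does. Nor do they settle whether recruitment should have continued.

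**What to change.** 1. In section 2.7.1, keep 30 per group (90 in total) as the planned size with its 80% power.
2. Beside it, report that 79 were randomised (26/27/26) against 90 evaluable required, with the power or the detectable difference at the achieved evaluable number. Name the method and give the planned-size figure by that same method. Until the evaluable number is known, the no-loss figures can be given as upper limits: about 72-73% (normal) or 69-70% (t), or a detectable difference at 26 per group of 8.7 or 8.9 mm³. Label any scan-loss rate as assumed.
3. Replace the Discussion sentence with one saying that the recruitment target was not reached and that power for the primary pairwise comparisons is below the planned 80%.

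The cost is a few sentences. No change to the design, data collection or analysis is involved. The article's statement about power becomes less favourable.

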### Study Design

2.1

The VOLTAIRE trial is a prospective, three‐arm, parallel‐group, randomized controlled trial. Participants are randomized (1:1:1) to: (1) risk factor counseling plus CTCA plaque burden, (2) risk factor counseling plus PRS information, or (3) standard risk factor counseling (control). The study is being conducted at a single site in a metropolitan hospital in Melbourne, Australia, with follow‐up assessments at 6 and 12 months. Recruitment targets individuals with T2D via diabetes outpatient clinics, general practice networks, and community advertisements (flyers, social media) around the hospital and co‐located university campus. This strategy enables a diverse patient sample and supports generalizability. While hospital‐based recruitment may bias toward patients engaged with healthcare, inclusion of community participants and quota sampling for gender balance mitigate this risk. An overview of the trial is presented in Figure 1.

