#### Statistical Methods

2.7.2

Analyses will follow a pre‐defined statistical analysis plan on an intention‐to‐treat basis, with two‐sided tests and a significance level of *α* = 0.05. Descriptive statistics will summarize socio‐demographic, clinical, and health profiles. Categorical data will be presented as frequencies and compared using chi‐square tests, reporting odds ratios and 95% confidence intervals. Continuous variables will be presented as either mean with standard deviation or median with interquartile range, with group comparisons via independent *t*‐tests or Mann‐Whitney *U* tests as appropriate.

Primary and secondary endpoints between groups at 12 months will be analyzed using mixed‐effects models, adjusting for baseline values and relevant socio‐demographic confounders, to assess treatment effects over time. Implementation objectives will be evaluated using a mixed methods approach: a 19‐question survey (including two free‐text sections) and focus groups (5–10 participants per intervention group), with qualitative data analyzed thematically.

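### The 0.83% Bonferroni level in the sample size equals 0.05/6, but three arms and one primary outcome support only three pairwise tests (two-sided 1.67%); the slip is conservative and its derivation is not stated.

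*Protocol article*

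**What the plan says.** All references are to the Protocol article.

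- Study Design (2.1): "The VOLTAIRE trial is a prospective, three‐arm, parallel‐group, randomized controlled trial", allocated 1:1:1.
- Outcomes (2.4): "The primary outcome is change in non‐calcified plaque volume on CTCA at 12 months". This is one outcome at one time point. The CTCA section (2.3.2) has scans only at baseline and 12 months.
- Sample Size Calculation (2.7.1): the size is "based on the objective to compare progression rates across the three groups". It asks for 30 evaluable participants per group (90 in total), giving 80% power for a difference of 8 mm³ between a pair of groups with a standard deviation of 11 mm³. The level is described as Bonferroni-"adjusted alpha of 0.83%, and that baseline adjustment accounts for" one-third of outcome variability.
- Statistical Methods (2.7.2): analyses will be done "with two‐sided tests and a significance level of" 0.05, under a pre-defined analysis plan that is not shown.
- Participants (2.2): recruitment has ended, with 79 randomized (26, 27 and 26).

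The article gives neither the number of comparisons behind 0.83% nor whether the figure is one- or two-sided.

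**The concern.** A Bonferroni level is the overall level divided by the number of tests. Three arms give three pairs, so two-sided 0.05 becomes 1.67% per pair. If only the two comparisons with control counted, it would be 2.5%. A level of 0.83% needs six tests, and the article describes no family of six. It is also 0.025/3, the per-tail level of a correct two-sided 1.67% test. That suggests a halving for two-sidedness was followed by a second halving when the figure was entered as a two-sided alpha.

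The primary power statement rests on this number. If 0.83% is carried into the analysis as a two-sided threshold, more than half of the permitted family-wise error goes unused. That would cost power in a trial that randomized 79 against 90 evaluable required.

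**Working it through.** **Inputs** (2.7.1 unless noted): difference 8 mm³; SD 11 mm³; one-third of variance removed by baseline adjustment; 30 per group; 80% power; level 0.83%. Two-sided tests at 0.05 come from 2.7.2.

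**Candidate levels**
- 0.05/3 = 0.01667 (1.67%)
- 0.05/6 = 0.00833 (0.83%)
- 0.025/3 = 0.00833 (0.83% per tail, i.e. two-sided 1.67%)

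**Residual variance.** 121 × 2/3 = 80.67, so the residual SD is 8.98 mm³.

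**Formula (normal approximation).** n per group = 2 × (z₁₋α/₂ + 0.842)² × 80.67/64 = 2 × (z₁₋α/₂ + 0.842)² × 1.2604.

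**Reproducing the plan's figure, with 0.83% as a two-sided level.** z = 2.638, so n = 2 × (2.638 + 0.842)² × 1.2604 = 30.5. At 30 per group the standard error of the difference is 8.98 × √(2/30) = 2.319 and the standardized difference is 8/2.319 = 3.450. Power is Φ(3.450 − 2.638) = 79.1%. This is the closest match to the stated 30 and 80%.

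**Two-sided 1.67%, which is the same as 0.83% per tail.** z = 2.394, so n = 2 × (2.394 + 0.842)² × 1.2604 = 26.4. Power at 30 per group is Φ(3.450 − 2.394) = 85.4%.

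**Both levels side by side.** The t figures use the noncentral t; each range runs from two-group to three-arm pooled degrees of freedom.

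| | two-sided 0.83% | two-sided 1.67% |
|---|---|---|
| n per group for 80%, z | 31 | 27 |
| n per group for 80%, t | 32–33 | 28 |
| Power at 30 per group, z | 79% | 85% |
| Power at 30 per group, t | 76–77% | 83–84% |
| Power at 26 per group, z | 72% | 79% |
| Power at 26 per group, t | 68–69% | 77–78% |

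At 26 per group the standardized difference is 8/(8.98 × √(2/26)) = 3.212. These rows assume that every randomized participant has two evaluable scans, so they are upper limits.

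**Family-wise error for three pairs** (large-sample, equal groups, all means equal): about 2.3% at two-sided 0.83% and about 4.4% at two-sided 1.67%.

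**The case against.** The strongest reply is that 0.83% is exactly 0.025/3. If it was meant per tail, the level is correct for three pairs and only the label is missing. On that reading 27 (z) or 28 (t) per group are needed, and 30 could be a rounding up, with 80% power met with some margin. On the two-sided reading, by contrast, 30 falls slightly short of 80%. So neither reading reproduces the stated figures exactly. This stands: the double halving is the closest numerical fit but is not established. The reply still leaves something to correct, because the article does not call 0.83% one-sided, and on that reading the power for 30 per group is 83–85%, not 80%.

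A second reply is that 0.83% is only a sizing assumption. This also stands. A reader might infer that 0.83% is the trial's decision threshold and that power will be lost in the analysis. The article does not say so: Statistical Methods gives 0.05 and refers to an analysis plan, which may fix the multiplicity rule. The power loss is therefore conditional on 0.83% being carried forward.

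A reader might also infer that this figure undersized the trial or raises the false-positive risk. It does neither. A stricter level asks for more participants, and family-wise error stays below 5%. The gap between 79 randomized and 90 evaluable comes from recruitment, not from this number.

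**Conclusion.** The level is wrong as written for the design described. The article supports at most three pairwise tests of one primary outcome, for which two-sided Bonferroni is 1.67%, half as strict as the printed 0.83%. Most likely the level was halved twice; otherwise a per-tail level is printed without its label and the power is understated.

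The error is conservative. The sample size is overstated by about 4 per group (30.5 against 26.4). Used as a two-sided threshold, 0.83% would cost about 6 to 7 points of pairwise power at 30 per group and about 8 to 9 points (t) at 26.

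These figures take the stated difference, SD and one-third variance reduction as given, and a family of all three pairs. It is a point worth correcting, but not a threat to the trial's type I error.

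**What to change.** Before unblinding:

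1. State how many primary comparisons form the family, and whether the adjusted level is two-sided or per tail.
2. For three pairs, replace 0.83% with two-sided 1.67%, or keep 0.83% and label it explicitly as the per-tail level.
3. Restate pairwise power at that level: about 83–85% for 30 evaluable per group, and at most about 77–79% for 26 per group if all randomized participants have evaluable serial scans.
4. Name the same threshold for the primary pairwise tests, since Statistical Methods gives only 0.05.

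Because recruitment has closed, the change should be dated and shown to precede any unblinded comparison, so that it cannot be read as a threshold loosened after seeing results. If the full protocol or analysis plan already derives 0.83%, for example from a larger family of tests, that derivation should be given instead. The cost is one number, one power statement and one sentence on the analysis threshold, with no additional participants.
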